## Abstract

**Background:**

COVID-19 poses a global health challenge with more than 325 million cumulative cases and above 5 million cumulative deaths reported till January 17, 2022, by the World Health Organization. Several potential treatments to treat COVID-19 are under clinical trials including antivirals, steroids, immunomodulators, non-specific IVIG, monoclonal antibodies, and passive immunization through convalescent plasma.

The need to produce anti-COVID-19 IVIG therapy must be continued, alongside the current treatment modalities, considering the virus is still mutating into variants of concern. In this context, as the present study will exploit pooled diversified convalescent plasma collected from recovered COVID-19 patients, the proposed hyperimmune Anti-COVID-19 intravenous immunoglobulin (C-IVIG) therapy would be able to counter new infectious COVID-19 variants by neutralizing the virus particles. After the successful outcome of the phase I/II clinical trial of C-IVIG, the current study aims to further evaluate the safety and efficacy of single low dose C-IVIG in severe COVID-19 patients for its phase II/III clinical trial.

**Methods:**

This is a phase II/III, adaptive, multi-center, single-blinded, randomized controlled superiority trial of SARS-CoV-2 specific polyclonal IVIG (C-IVIG). Patients fulfilling the eligibility criteria will be block-randomized using a sealed envelope system to receive either 0.15 g/Kg C-IVIG with standard of care (SOC) or standard of care alone in 2:1 ratio. The patients will be followed-up for 28 days to assess the primary and secondary outcomes.

**Discussion:**

This is a phase II/III clinical trial evaluating safety and efficacy of hyperimmune anti-COVID-19 intravenous immunoglobulin (C-IVIG) in severe COVID-19 patients. This study will provide clinical evidence to use C-IVIG as one of the first-line therapeutic options for severe COVID-19 patients.

**Trial registration:**

Registered at clinicaltrial.gov with NCT number NCT04891172 on May 18, 2021.

## Administrative information

Note: the numbers in curly brackets in this protocol refer to SPIRIT checklist item numbers. The order of the items has been modified to group similar items (see http://www.equator-network.org/reporting-guidelines/spirit-2013-statement-defining-standard-protocol-items-for-clinical-trials/).

## Introduction

### Background and rationale {6a}

On March 11, 2019, the World Health Organization declared COVID-19 as a pandemic [1]. Severe acute respiratory syndrome coronavirus 2 (SARS-CoV-2) is the causative agent of this systemic disease. COVID-19 has been categorized as a biphasic illness with an early phase of viral replication and second phase directed by host immune response [2]. This second phase may lead to severe and critical COVID-19 cases progressing towards a life-threatening multiple organ dysfunction, characterized by refractory hypoxemia due to acute respiratory distress syndrome (ARDS) [3].

Despite the global and continuous efforts of researchers to combat COVID-19 including provision of vaccines to the mass population, there is still a surge in COVID-19 cases due to emergence of new variants of the SARS CoV-2 making vaccines less effective. This emphasizes the need to develop broadly protective interventions against the evolving pandemic [4]. Convalescent plasma (CP) from recovered patients has been used previously as a passive immunotherapy in epidemics associated with coronaviruses, SARS CoV-1 in 2003, Middle East respiratory syndrome (MERS) in 2012, and also in the current COVID-19 pandemic [5]. Intravenous immunoglobulin (IVIG) extracted from CP is recommended for the treatment against a variety of inflammatory, infectious, autoimmune, and viral diseases including SARS and MERS [6, 7]. IVIG helps in regression of disease from multiple fronts including virus neutralization and immunomodulation through anti-cytokine activity and prevention against other superimposed bacterial infections due to the polyclonal formulation of the drug [8–10]. Hyperimmune anti-COVID-19 intravenous immunoglobulin (C-IVIG) is an unexplored therapy amidst the rapidly evolving spectrum of medical therapies for COVID-19 and is expected to counter the three most life-threatening consequences of COVID-19 including lung injury by the virus, cytokine storm, and sepsis [11].

Despite great interest, due to lack of availability of clinical evidence for the safety and efficacy of hyperimmune IVIG in COVID-19 patients, the use of hyperimmune intravenous immunoglobulin as one of the first-line therapeutic options against COVID-19 has been limited. In this context, an adaptive phase II/III, multicenter center, single-blinded superiority trial has been designed to assess the safety and efficacy of single dose of hyperimmune anti-COVID-19 intravenous immunoglobulin (C-IVIG) in severe COVID-19 patients after observing safety and efficacy of C-IVIG in phase I/II clinical trial of severe and critical COVID-19 patients [11].

### Objectives {7}

This trial aims to investigate the safety and clinical efficacy of hyperimmune anti-COVID-19 Intravenous Immunoglobulin (C-IVIG: 5% liquid formulation), on severe COVID-19 patients.

### Trial design {8}

This is an adaptive, phase II/III, multi-center, randomized controlled, single-blinded superiority trial with parallel group design to assess the safety and efficacy of single dose of C-IVIG in patients with symptoms of severe COVID-19. Eligible participants will be randomly assigned in 2:1 ratio (206 tests: 103 controls) by block randomization method to receive C-IVIG plus standard of care (intervention group) or only standard of care (control group). The adaptive study design refers to adapting the strategy of trial based on interim analysis at three particular time points [12]. Outcome of the interim analysis will lead to making decision for terminating trial in case of serious adverse events or selecting a higher C-IVIG dose regime in case selected dose of C-IVIG (0.15g/Kg) not found efficacious. A flow chart of the trial design is shown in Fig. 1.

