#### Interim analyses {21b}

An interim analysis will be performed after recruitment of 15%, 30%, and 60% participants in the trial. It will assess primary outcomes of the study particularly focusing on the safety and efficacy of the infused drug. Safety of the intervention will be monitored in terms of any immediate or serious adverse event that can be observed after the administration of the drug. The efficacy of the intervention will be noted in terms of the patient's improvement in clinical status as compared to the control group.

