## Discussion

This phase II/III clinical trial is an adaptive, randomized controlled, multi-center, single-blinded superiority trial of SARS-CoV-2 specific polyclonal IVIG (C-IVIG) versus standard of care for patients hospitalized with severe COVID-19. Single dose of C-IVIG in combination with the standard of care was found to be both safe and efficacious in our previous clinical trial phase I/II while increasing the survival rate and reducing the risk of disease progression [13]. There were no significant changes observed when different doses of C-IVIG were compared in the phase I/II; however, it was found that C-IVIG dosage of 0.15 g/kg have significantly improved the therapeutic response in severe COVID-19 patients. These results warrant the phase II/III clinical trial study of C-IVIG, in order to evaluate its safety and efficacy in large sample size by comparing outcomes (28-mortality, hospital stay and drug-related adverse events) of C-IVIG along with SOC in intervention group and SOC only in comparator group provided during the hospital stay.

Study participant selection for this study is based on the results of our previous clinical trial where severe patients had 100% survivability and early hospital discharge than critical patients and comparator group. We evaluated that hospital stay, reliance on mechanical ventilation, and burden on hospital could be reduced if C-IVIG is administered to the severe COVID-19 patients by delaying the disease progression.

This is an adaptive clinical trial to investigate the risk-benefit analysis of C-IVIG administration for severe COVID-19 at first and second interim of the study. Major outcome variables to be assessed for interim analysis are adverse events, 28-day mortality, and change in clinical status of the patients. Fate of this clinical trial is based on whether the C-IVIG is safe and efficacious. If the treatment modality is found to be safe but not efficacious as compare to comparator group, we might select different dosage of C-IVIG for further study participants; if interim analysis indicate association of serious adverse events with administration of C-IVIG or with significant high mortality ratio in intervention group than comparator group or if incidence rate of COVID-19 is low till the study completion date, then this clinical trial would be early terminated due to aforementioned reasons.

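### If an interim look raises the dose for later patients, the single C-IVIG v control comparison mixes two doses, and the measure that triggers the change is stated in two ways

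*Protocol article*

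**What the plan says.** **Dose change.** Trial design {8} allows for "selecting a higher C-IVIG dose regime in case selected dose of C-IVIG (0.15g/Kg) not found efficacious". Section {11b} adds that the higher dose will be one already studied in phase I/II. The Discussion, more loosely, says "we might select different dosage of C-IVIG for further study participants". The change therefore happens inside this trial.

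**Everything else assumes one dose.** The Abstract and sections {6b} and {11a} set the intervention at a single 0.15 g/kg dose. Section {14} sizes one contrast, 206 v 103. Section {20a} puts all randomised patients in the intention-to-treat population and compares time to the primary end point between the two groups. Section {20b} plans no subgroup analyses, and {20c} makes intention to treat primary.

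**Looks.** Trial design {8} speaks of "adapting the strategy of trial based on interim analysis at three particular time points", and Interim analyses {21b} says "An interim analysis will be performed after recruitment of 15%, 30%, and 60% participants in the trial". The Discussion places the "risk-benefit analysis of C-IVIG administration for severe COVID-19 at first and second interim of the study".

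**Measure.** Section {21b} says of the interim analysis: "It will assess primary outcomes of the study particularly focusing on the safety and efficacy of the infused drug". The primary outcome in {12} is 28-day all-cause mortality. The same section then notes efficacy by "improvement in clinical status as compared to the control group", which {12} lists as a secondary outcome. The Discussion says: "Major outcome variables to be assessed for interim analysis are adverse events, 28-day mortality, and change in clinical status of the patients".

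**The concern.** The dose change is a planned adaptation, but the analysis that the article describes has only two groups. Followed as written, a switch leaves one C-IVIG group made up of patients on a dose that the trial has just judged not efficacious and patients on another dose. The weights depend on when the switch happened to fall. A reader could take the single result as the effect of 0.15 g/kg, which the trial was set up to test, or of the higher dose, which would be the one carried forward. If the doses differ, it is neither.

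The efficacy measure matters because it drives the switch. Mortality and clinical status can point in different directions at the same look, and the text does not settle which one decides.

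**Working it through.** **1. The plan's own sample size.** Inputs from {14}: survival 75% v 40%, power 90%, ratio 2:1, margin 0.15, dropout 30%. With unpooled variances:

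n(control) = [0.40×0.60 + (0.75×0.25)/2] × (z_α + z_0.90)² / (0.75 − 0.40 − 0.15)²

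At one-sided 0.05 this is 0.33375 × (1.645 + 1.282)² / 0.04 = 71.45, so 72 controls and 144 C-IVIG patients. Dividing by 0.70 gives 103 and 206, total 309, which matches the plan. (The stated 99% confidence level does not give 309; that is a separate matter.) The formula contains one C-IVIG group with one effect.

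**2. Patients at each look.** 309 × 0.15, 0.30 and 0.60 = 46, 93 and 185. Two thirds are on C-IVIG.

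| Switch at look | C-IVIG on 0.15 g/kg | C-IVIG left for the new dose | Controls before / after |
|---|---|---|---|
| 1 | 31 | 175 | 15 / 88 |
| 2 | 62 | 144 | 31 / 72 |
| 3 | 124 | 82 | 61 / 42 |

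**3. What the pooled difference shows.** With effects d_low and d_high, and n the number on the low dose, pooled difference = d_low × n/206 + d_high × (1 − n/206). Take d_low = 0 and d_high = 35 points, an assumed extreme case using the plan's own difference:

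- look 1: 35 × (1 − 31/206) = 29.7 points
- look 2: 35 × (1 − 62/206) = 24.5 points
- look 3: 35 × (1 − 124/206) = 13.9 points

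If d_low = d_high, the formula returns that common value and nothing is lost.

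**4. Precision of 0.15 g/kg against same-period controls.** 95% half-width = 1.96 × √(0.75×0.25/n_T + 0.40×0.60/n_C), at the planned 75% v 40%:

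- 31 v 15: 29 points
- 62 v 31: 20 points
- 124 v 61: 14 points
- 206 v 103, for comparison: 11 points

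For the higher dose the same formula gives 12 points (175 v 88), 13 (144 v 72) and 18 (82 v 42).

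**5. Error rate of dose-specific claims.** Two tests at two-sided 0.025 sum to at most 0.05. In 400,000 simulated trials with no effect of any dose (survival 60% in both groups, assumed), the overall error was 0.049 when the dose always changed once. When it changed only if survival was no better than control, with 0.05 kept for trials without a change, the error was 0.050. With a change at every look (four doses, each at 0.025), it was 0.094.

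**6. Selection bias.** At an assumed true 75% v 60%, the mean 0.15 g/kg estimate, given survival no better than control at look 1, is −8 points against a true +15.

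**The case against.** **No sentence orders pooling.** This is true. The full protocol or an analysis plan, neither shown, could split the analysis by dose. It limits the point to what the article fixes: a two-group intention-to-treat comparison beside a planned dose change, with subgroup analyses ruled out.

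**The objective in {7} names C-IVIG and no dose, so a pooled contrast answers it.** This stands in part. The pooled result is a legitimate answer about C-IVIG as given. It is not an answer about 0.15 g/kg, which the Abstract and {11a} set as the intervention.

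**The doses may not differ.** The Discussion reports no significant change between doses in phase I/II. If effects are equal, pooling does no harm. But a switch for lack of efficacy makes sense only if a higher dose is expected to do better.

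**A switch is unlikely.** No threshold is given, so its probability cannot be stated. As an illustration, if the trigger were survival no better than control, the exact binomial probabilities at 75% v 40% are 1.0%, 0.06% and under 0.001% at the three looks. At an assumed 75% v 60% it is 14.6% at look 1.

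**The measures overlap.** The seven-category scale includes death, and the Discussion lists both measures. That softens the conflict but does not resolve it: {21b} opens with the primary outcome and then judges efficacy by a secondary one.

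**Stronger readings.** A reader might infer that the pooled test has an inflated error rate. It does not if no dose works, because allocation stays 2:1 with concurrent controls overall. A reader might infer that looks set by recruitment decide on incomplete day-28 data. With a cut at the mark and uniform accrual over about 460 days (assumed), 309/460 × 28, or about 19 patients, would lack day-28 status, which is 41%, 20% and 10% of those recruited. But the article fixes no data cut. A reader might also infer that the third look cannot change the dose. The Discussion does not say so; its mention of two looks is loose wording beside the three in {8} and {21b}.

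**Conclusion.** The point holds as a conditional one. If the dose is changed and the doses differ in effect, the only comparison the article describes yields a mixture weighted about 15:85, 30:70 or 60:40 (0.15 g/kg to higher dose), depending on the look. The gap between 35 points and the 30, 24 or 14 shown rests on the assumed extreme case; with closer effects it shrinks in proportion. What is at stake is the meaning of the estimate, not the validity of the test. The double statement of the interim efficacy measure is a genuine inconsistency within {21b}. The count of looks is a wording slip. Moving the dose decision to day 28, using mortality as the sole measure and allowing only one change are design options with costs of their own; the text does not show their absence to be an error. This should be fixed, but it does not undermine the trial if the dose stays at 0.15 g/kg.

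**What to change.** - State that, if the dose changes, each dose is estimated against controls randomised in the same period.
- Test dose-specific claims at two-sided 0.025 each. This suits one change; more doses need a further split of 0.05. The split covers only the dose-specific claims, not an added claim from the pooled test.
- Report the pooled result as the effect of C-IVIG given as a mixed regimen, not of 0.15 g/kg.
- Make {21b} and the Discussion name the same efficacy measure for the dose decision, and align the Discussion with the three looks in {8} and {21b}.

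**Cost.** This takes a protocol amendment with approval under {25}, and no new data. Dose-specific estimates are less precise, with the half-widths shown above. The 0.15 g/kg estimate after a switch is biased low because it follows a poor look, and should be reported with that caution.

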**Fig. 1 Fig1:**
[figure not shown]
Consort flow diagram of the trial design

## Methods: participants, interventions, and outcomes

### Study setting {9}

The trial will be conducted in Karachi, Pakistan at Dow University of Health Sciences (Ojha Campus) and Sindh Infectious Disease Hospital and Research Center (SIDH).

### Eligibility criteria {10}

#### Participant selection

A total of 309 participants from both male and female gender will be recruited according to the following inclusion and exclusion criteria.

Inclusion criteria for participant:Study participants should be above 18 years of ageHave positive SARS-CoV-2 PCR on nasopharyngeal and/or oropharyngeal swabsClassified as severe COVID-19 according to WHO guideline (5L-15L of oxygen requirement on face mask (FM), Non-rebreather mask (NRM)Have signed the consent to participate in the study

Exclusion criteria for participants:Participants will be excluded if they have critical COVID-19 [non-invasive ventilation (HFNC, BiPAP, CPAP) and invasive ventilation]Pregnant femalesPrevious allergic reaction to immunoglobulin treatmentKnown case of any autoimmune disorderChronic renal diseaseKnown case of thromboembolic disorderAseptic meningitis

#### Who will take informed consent? {26a}

Consent will be taken by the Clinical Research Associate, or the treating physician on a document designed as per guidelines of Drug Regulatory Authority of Pakistan (DRAP). The participant itself or first-degree relative is eligible to provide consent.

#### Additional consent provisions for collection and use of participant data and biological specimens {26b}

Provisions to collect and use participant’s data and biological specimens are mentioned in informed consent form.

### Interventions

#### Explanation for the choice of comparators {6b}

The intervention group will receive a single dose of C-IVIG (0.15 g/Kg) along with standard hospital care and participants will be assigned in a sequential manner. C-IVIG is a 5% concentrated preparation of anti-SARS-CoV-2 antibodies purified from fractionation of pooled convalescent plasma of COVID-19 survivors [13]. Hyperimmune C-IVIG was selected for evaluation as it has not yet been used as a treatment modality for severe COVID-19 patients, although multiple clinical trials to assess convalescent plasma and immunoglobulins as therapeutic options for COVID-19 are being conducted globally. C-IVIG when infused in COVID-19 patients is expected to regulate disease progression via multiple mechanisms including SARS-CoV-2 neutralization, immunomodulation to prevent cytokine storm, and prevention of superimposed bacterial infection (sepsis) due to presence of polyclonal antibodies against other endemic pathogens [11]. C-IVIG is assumed to contain polyvalent antibodies against SARS-CoV-2 and other co-existing infections with no drug-related adverse events observed, hence a potential and safer treatment modality for COVID-19. The lower dose of C-IVIG (0.15 g/Kg) was selected due to its proven safety and efficacy for severe COVID-19 patients in phase I/II clinical trial [11]. The control group will receive standard hospital care only. Participants will be assigned in a sequential manner in both groups.

#### Intervention description {11a}

Intervention group will receive a single dose of 0.15 g/kg body weight C-IVIG along with standard care. Control arm will receive standard hospital care only. The dose will be administered intravenously with a flow rate of 20 ml/h in the first hour and 25 ml/h till the dosage end. Standard hospital care includes airway support, anti-viral medication, antibiotics, fluid resuscitation, hemodynamic support, steroids, painkillers, and anti-pyretic. Standard of care will ensure blinding because as part of the usual hospital care severe COVID-19 patients is given multiple infusion, and hence, it will not be possible for patients in intervention group and control group to discriminate between standard of care and C-IVIG infusion.

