#### Criteria for discontinuing or modifying allocated interventions {11b}

Modification of the allocated intervention will be based on the planned interim analysis. Outcome of the interim analysis will lead to making decision regarding selection of higher C-IVIG dose in case of currently selected 0.15 g/kg dose not found efficacious. The higher dose of C-IVIG will be selected from the dosage investigated in previous phase I/II clinical trial [11]. The C-IVIG infusion will be discontinued if any serious adverse event occurs or discontinued on patient request and the patient will be excluded from the study.

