### Assignment of interventions: blinding

#### Who will be blinded {17a}

This is a single-blinded trial in which trial participants are blinded.

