### Data collection and management

#### Plans for assessment and collection of outcomes {18a}

Outcome, baseline, and other trial data will be collected by the study investigators. The clinical research associate will check the data. Nasopharyngeal/oropharyngeal swabs and blood samples will be sent to DUHS laboratory, where tests will be performed according to laboratory standard operating procedures (SOPs). Data reports can be found on HMIS (Hospital Management information system) and will be collected on clinical research forms (CRF).

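### The participant blind is stated as a certainty that the design does not support, and judgement-based secondary outcomes are recorded by staff who know the arm

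*Protocol article*

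**What the plan says.** Intervention description {11a} rests the blind on routine care: "Standard of care will ensure blinding because as part of the usual hospital care severe COVID-19 patients is given multiple infusion". From this it concludes that "it will not be possible for patients in intervention group and control group to discriminate between standard of care and C-IVIG infusion". The same section gives the arms as "Intervention group will receive a single dose of 0.15 g/kg body weight C-IVIG along with standard care" and "Control arm will receive standard hospital care only". The article describes no sham infusion and no masking of bag or line.

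Who will be blinded {17a} states: "This is a single-blinded trial in which trial participants are blinded". Procedure for unblinding {17b} confirms that nobody else is. Sequence generation {16a} gives the site investigator access to the allocation sequence, and Implementation {16c} has investigators assign treatment. Plans for assessment and collection of outcomes {18a} adds: "Outcome, baseline, and other trial data will be collected by the study investigators". No blinded assessor is named for any outcome.

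Interim analyses {21b} measures efficacy by "improvement in clinical status as compared to the control group". The Discussion lists adverse events, 28-day mortality and change in clinical status as the main interim variables. A finding of safe but not efficacious may lead to a different dose for later participants.

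**The concern.** There are two linked problems.

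First, the assurance is absolute, but its only support is that patients have other infusions running. That may make an extra infusion harder to notice. It does not make it impossible to notice when one arm has the infusion and the other has no counterpart.

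Second, even a perfect participant blind would not protect outcomes that staff decide or rate. Below death, the seven-category scale turns on whether the patient is in hospital, which oxygen or ventilatory support is in use, and whether activities are limited. Radiological findings depend on a reader. If the people who make or record these judgements know the arm, the comparison can shift without any drug effect. What is at stake is the credibility of those secondary efficacy results and of the clinical-status component of the interim assessment.

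**Working it through.** No sample size, power or error rate enters this point. The check compares sections, with a little arithmetic on the infusion and on the interim looks.

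**1. What the treated arm gets that the control arm does not.** Inputs: 0.15 g/kg, 20 ml/h for the first hour and 25 ml/h afterwards (Intervention description {11a}); 5% preparation (Explanation for the choice of comparators {6b}), taken as 0.05 g/ml. Body weight is not given, so 50 to 90 kg is assumed.

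- Volume per kg = 0.15 / 0.05 = 3 ml/kg.
- Duration = 1 h + (volume − 20) / 25 h.

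| Assumed weight | Volume | Duration |
|---|---|---|
| 50 kg | 150 ml | 1 + 130/25 = 6.2 h |
| 70 kg | 210 ml | 1 + 190/25 = 8.6 h |
| 90 kg | 270 ml | 1 + 250/25 = 11.0 h |

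The treated arm has one additional slow infusion of roughly 6 to 11 hours. The article does not give the number, volume or duration of standard-care infusions, so this does not show that patients would notice. It shows that the claim of impossibility has no demonstrated basis.

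**2. Who knows the allocation and who records outcomes.** Sections {17a} and {17b} blind patients only. Sections {16a} and {16c} put the sequence and the assignment with investigators, and {18a} puts outcome collection with study investigators. The concealment text in {16b} concerns ignorance of the sequence before the envelope is opened, not masking afterwards. Section {20a} says the data to be analysed will be blinded. That acts after outcomes have been recorded, so it cannot correct a judgement already made.

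**3. Which outcomes are exposed.**

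| Outcome | Exposure to knowledge of the arm |
|---|---|
| 28-day all-cause death (primary) | Ascertainment little affected |
| CRP, IL-6, antibody levels | Laboratory measurements, little affected |
| Ordinal categories 1 to 6 | Depend partly on staff decisions or ratings |
| Radiological findings | Depend on a reader; masking not stated |

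**4. Where this meets the interim looks.** The looks are at 15%, 30% and 60% of 309 participants:

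- 0.15 × 309 = 46.35, about 46 patients (about 31 v 15).
- 0.30 × 309 = 92.7, about 93 patients (about 62 v 31).
- 0.60 × 309 = 185.4, about 185 patients (about 124 v 62).

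At each look the efficacy measure named in {21b} is clinical status, which is collected without masking. Mortality and adverse events are assessed alongside it.

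**The case against.** The strongest reply is that the design is openly disclosed. Sections {17a} and {17b} say plainly that only patients are blinded, and a staff-open trial with all-cause mortality as primary outcome is a recognised choice. That stands. The fault is not single-blinding itself but the certainty attached to it and the lack of masking for outcomes that need judgement.

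A second reply is that collecting is not assessing. Sections {18a} and {19} describe retrieval from the hospital information system and files, entry by designated personnel, a check by the research associate, and laboratory tests under standard procedures. This stands for the laboratory measures. It does not answer for discharge, choice of support, activity limitation or image reading. The article does not say who reads images or whether readers know the arm. Nor is it clear how far the ordinal scale is rated after discharge, since its time frame mentions both 28 days and the hospital stay. A journal article may also leave bag or line masking to the full protocol; if such masking exists, it should be cited as the basis for the claim.

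A reader might infer a contradiction from {11b}, where the C-IVIG infusion may be "discontinued on patient request", as if the patient must know which infusion it is. The text does not support that. It is ordinary right-to-stop wording, and a patient can ask for an infusion to stop, or leave the study, without knowing which bag holds the study drug.

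A reader might also take the first look, with about 15 controls, and note that reclassifying one of them moves that arm's rate by 1/15 = 6.7 percentage points. That is the granularity of a small group under a two-way split into improved and not improved, which the article does not define. It does not measure bias.

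Finally, bias in favour of C-IVIG would not produce an early efficacy claim, because no early stop for efficacy is described. It would make a finding of no efficacy, and hence a dose change, less likely.

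**Conclusion.** The concern holds in limited form. The assertion that patients cannot tell the arms apart is stronger than the design supports: the participant blind is plausible but not assured. Separately, ordinal clinical status other than death, radiological findings and the clinical-status part of the interim efficacy assessment are open to assessment bias, because the investigators who collect outcomes know the allocation.

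The documents do not support a reading that the whole trial is compromised, or that clinical status alone drives the interim decisions. The size of any bias cannot be derived from the document.

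The conclusion rests on the article as shown, which describes no matching infusion and no masked assessor. The infusion figures also rest on assumed body weights and on reading 5% as 0.05 g/ml. The point merits correction, but it does not threaten the ascertainment of the primary outcome.

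**What to change.** 1. In Intervention description {11a}, replace the certainty with a statement that the participant blind is not assured and that staff are unblinded.
2. Have the existing readers read radiological images under study number, with the arm withheld.
3. Have the post-discharge calls in Plans to promote participant retention and complete follow-up {18b} made by existing designated staff who do not see the allocation.
4. Take in-hospital ordinal categories from the hospital information system or chart record at a fixed time. State that this removes rating bias but leaves unblinded choice of device and discharge untouched.

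The cost is a change of wording and some reassignment of tasks among existing staff, with no new assessor. Arm labels must be kept off imaging requests and away from callers, and a fixed scoring time must be observed, which takes some discipline in a staff-open trial. The blinding claim becomes more modest.
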